## Abstract

**Methods and Analysis::**

In the present randomized controlled study, 296 patients with confirmed clinical pregnancy following IVF-ET will be randomly assigned to receive standard intervention support or WeChat peer support on a 1:1 basis. The levels of anxiety and depression are the primary endpoints. Assessments will be performed at baseline measurements, first trimester, second trimester, and third trimester, and data will be collected.

**Ethics and Dissemination::**

This study has been approved as ethical by the affiliated hospital of Shandong University of Traditional Chinese Medicine’s Reproductive Ethics Committee. Each patient will sign a written statement of informed permission. All information and biological samples will be legally protected. A peer-reviewed academic journal will publish the findings of this investigation.

**Discussion::**

Given the inconvenience of visits due to the current pandemic of COVID-19, this study addresses the patient’s visit needs by combining WeChat, the most widely used social software in China, with peer support, while helping improve maternal anxiety, depression, and pregnancy outcomes following IVF-ET.

## 1. Introduction

The COVID-19 outbreak has had a substantial impact on patient medical treatment procedures as well as emotional and mental health states. Home isolation decreases patients’ compliance with medical care and medicines, and it also raises some residents’ anxiety, despair, sleep problems, and other negative emotions, according to a poll.^[1,2]^ Psycho-emotional disorders in infertility patients have gotten more attention as the medical paradigm evolves from biomedical to bio-psycho-social,^[3–5]^ and these unpleasant emotions may cause varied degrees of melancholy, anxiety, pain, and a deterioration in life quality.^[6]^ Numerous studies have shown that advanced reproductive technology-seeking couples are more likely than naturally conceived couples to endure psychological anguish.^[7]^ The consumption of large amounts of time and money, the uncertainty surrounding the outcome of treatment, and the worries surrounding the course of treatment may all contribute to anxiety and depression. Additionally, anxiety over early parenting challenges, fetal survival, and pregnancy outcomes is also higher.^[8–12]^ These psychological aspects are crucial to in vitro fertilization and embryo transfer (IVF-ET) treatment and may even have an impact on pregnancy outcomes. Women undergoing IVF-ET may experience difficulty getting pregnant, and the psychological stress that follows pregnancy remains. Unfavorable feelings will adversely affect the development of the fetus and the maternal and fetal endocrine systems.^[13]^ The fetal nervous system’s development and the fetus’s functioning of the hypothalamic-pituitary-adrenal (HPA) axis have both been found to be negatively impacted by maternal anxiety, depression, and other negative emotions.^[14,15]^ As preterm deliveries, miscarriages, fetal intellectual disabilities, and congenital malformations are significantly higher in pregnant women, anxiety and depression are independent risk factors for poor pregnancy outcomes.^[16,17]^

It’s not a new concept to use peer support to recognize and treat various health concerns. A peer support program is a method used to enable people with similar illnesses, bodily problems, or experiences to help 1 another, as well as to provide social, emotional, and practical support.^[18]^ People with similar experiences are more able to bond, which can lead to more genuine empathy and validation, according to Mead and MacNeil’s “generic” definition.^[19]^ Self-regulation appears to be non-coercive, reciprocal, and decentralized and can be supported by social norms, identity, and friendship.^[20]^ Peer support is acknowledged for having a significant positive influence on underrepresented and difficult-to-reach groups and plays a role in humanizing healthcare.^[21]^ Self-management of chronic diseases such as cancer, diabetes, hypertension, etc, has been proven to improve patients’ physical, psychological, and health outcomes.^[22–24]^ There have been numerous studies regarding breastfeeding, all of which have shown positive results.^[25]^ A number of studies have demonstrated that, although a lack of social support is associated with depression and anxiety prenatally and postnatally, 1’s sense of other people’s availability as resources significantly increases 1’s capacity to regulate 1’s own distress.^[26–28]^ Several interrelated benefits of peer support have been identified as enhancing the emotional wellbeing of mothers during pregnancy and postpartum,^[21]^ as of yet, no studies have been conducted on pregnancies achieved through assisted reproduction.

In recent years, the Internet’s rapid development and the evolution of information technology have changed how medicine is practiced. A new word, e-health, is used to describe health services and information that are supplied or improved via electronic procedures and communications.^[29]^ In nations with limited medical resources, like China, high smartphone penetration and extensive adoption of social media applications present hitherto unheard-of prospects for mobile phone-based e-health interventions. Several studies have demonstrated the effectiveness of smartphones and social media in promoting health habits, which suggests that booming e-health can significantly impact chronic disease treatment.^[30,31]^ All in all, electronic medical care has been extremely important during the outbreak.

Mobile health apps are revolutionizing how doctors consult with patients in China. WeChat has grown to be the most popular and widely used social media platform in China and is an essential component of Chinese citizens’ daily lives.^[32]^ It is simple to use and offers group chats, text and voice messaging, free audio and video calls, access to official accounts and mini-programs, etc. WeChat makes getting health information more convenient, quick, and need-based. Numerous hospitals have implemented programs for health counseling, health evaluation, health education, and health promotion centered on helping patients with chronic illnesses live healthy lifestyles and eat sensibly while also fostering positive doctor-patient relationships. WeChat groups have been used to share disease-related information with patients, which has increased their medication compliance.^[33,34]^ Patients with chronic diseases can benefit from continuous, prompt, and thorough follow-up interventions in order to achieve the goals of early detection, early treatment, and early prevention. Data collected by WeChat can be efficiently gathered, a sizable database can be created, and data support can be provided to enhance diagnosis and treatment. In conclusion, WeChat-based health interventions are less expensive, more effective at getting patients to comply with their treatment plans, less likely to cause complications, and have higher follow-up rates. Thus, traditional medical resources are balanced, effective physician-patient communication is encouraged, and public resources are reduced.^[35–37]^

In contrast, research on WeChat group applications for pregnant women and assisted reproduction is scarce. Therefore, the aim of this study is to establish a WeChat group that provides peer support to pregnant women undergoing IVF-ET to assist them in coping with anxiety and depression during pregnancy. Consequently, it is expected to serve as a resource for clinical decision-making.

## 2. Methods and analysis

### 2.1. Study design

A randomized control trial design will be used in this study. It is anticipated that recruitment at the Reproductive Center of Integrated Medicine, Affiliated Hospital of Shandong University of Traditional Chinese Medicine (SDUTCM) will begin in December 2022 and last through December 2023 for women with confirmed clinical pregnancy undergoing IVF-ET. Writing this guideline, we adhered to SPIRIT’s suggestions.^[38]^ Figure 1 displays the research flow chart, and Table 1 displays the research process timetable.

**Table 1 T1:** Example template of recommended content for the schedule of enrolment, interventions, and assessments. *

Outcome	Assessment	Baseline	11–13 wks gestation	19–21 wks gestation	27–29 wks gestation	Within 3 d after delivery
**Primary outcome**						
Anxiety level	SAS core	√	√	√	√	√
Depression level	SDS core	√	√	√	√	√
**Secondary outcome**						
pregnancy outcome						
ectopic pregnancy			√	√	√	
miscarriage			√	√	√	
early pregnancy loss			√			
late pregnancy loss			√	√	√	
premature birth						√
live birth						√

SAS = self-rating anxiety scale, SDS = self-rating depression scale.

**Figure 1. F1:**
[figure not shown]
The study flow chart.

### 2.2. Data collection

Both groups of patients are required to provide baseline information, including sociodemographic characteristics, disease history, and social behavioral characteristics such as smoking and alcohol use. Collect and complete the self-rating anxiety scale (SAS), which consists of 20 items overall, of which 5 indicate positive emotional experience and 15 negative emotional experience; the greater the score, the more anxious the patient is; the score below 50 represents normal, while mild will be anxiety score of 50 to 59, moderate anxiety 60 to 69, severe anxiety 70 points or more, and self-rating depression scale (SDS) (a total of 20 items; the greater the score, the higher the level of anxiety). Less than 50 points are considered normal, 50 to 59 points are considered mild anxiety, 60 to 69 points are considered moderate anxiety, and more than 70 points are considered severe anxiety during the course of treatment.

### 2.3. Eligibility criteria

#### 2.3.1. Inclusion criteria.

Clinically pregnant women (i.e., fetal heartbeat or gestational sac at 6–9 weeks after embryo transfer^[39]^) undergoing IVF-ET.age 18 to 49 years old.SAS standard score ≥ 50 points (i.e., mild anxiety or above); SDS standard score ≥ 50 points (i.e., mild depression or above).Patients who own electronic devices such smartphones, tablets, or computers, have Internet access, and are skilled WeChat users.Have reading, writing, and comprehension abilities.Informed consent and willing participation for WeChat group-based peer support.

#### 2.3.2. Exclusion criteria.

Accompanied by other serious physical diseases, acute and chronic diseases or mental disorders, which affect compliance and follow-up.Those who are undergoing psychotherapy at the moment or taking part in comparable studies.There is cognitive dysfunction, or those with poor comprehension or language barriers.

#### 2.3.3. Dropout criteria.

After recruitment, participants who failed to comply with the clinical study protocol, did not match the inclusion criteria, did not follow conventional treatment practices, or refused to give their permission should be removed. Participants who fulfilled the eligibility requirements but withdrew from the clinical trial for a variety of causes, such as individuals who voluntarily withdrew or when the researchers became aware that the subjects had withdrawn.

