### 2.4. Study case discontinuation

Subjects will be removed from the study if they exhibit unusual physiological reactions, experience other unanticipated events, or are deemed unfit to continue taking part in the experiment. In the event that the individual experiences significant issues or if their health worsens, immediate action will be done.

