### 2.9. Randomization and blinding

After informed consent, subjects will be assigned 1:1 by computer to one of the WeChat group peer support group or the routine intervention group using a random code sequence in the order of registration. Randomization protocols are entered into the online central randomization database (www.medresman.org). Given the apparent difference in intervention strategies between the 2 groups, neither investigators nor participants were blinded; however, trial outcome assessors will be blinded.

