### 2.11. Sample size calculation

Overall effectiveness rate is defined as the proportion of patients whose SAS and SDS scores have reduced by more than 25%, the primary endpoint of the study. Based on previous clinical experience in our center, at the third follow-up visit, we found that the overall effectiveness rate was approximately 75% in the WeChat peer support group and about 60% in the routine intervention group. A total of 236 patients were enrolled in the study utilizing the PASS 15 procedure (NCSS, LLC. Kaysville, Utah), with a hypothesis test level of 0.05 and a test power of 0.8. After accounting for the 20% dropout rate, 296 patients with 148 in each group comprised the final sample size.

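### Women are to be removed on grounds that mostly arise after randomisation, and nothing keeps them in follow-up or in their assigned group; this breaks the randomised comparison and can bias it in either direction

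*Protocol article*

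**What the plan says.** Two sections of the protocol article order removal.

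- Section 2.3.3 (Dropout criteria) sets the time as after recruitment and lists "participants who failed to comply with the clinical study protocol, did not match the inclusion criteria, did not follow conventional treatment practices", together with refusal of permission, as grounds on which participants are to be removed. Its second sentence counts voluntary withdrawals as dropouts too.
- Section 2.4 (Study case discontinuation) adds a second rule: "Subjects will be removed from the study if they exhibit unusual physiological reactions, experience other unanticipated events, or are deemed unfit to continue". The removal is from the study, not only from the intervention.

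Three other places bear on the point.

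- Section 2.9 places allocation after consent ("After informed consent, subjects will be assigned 1:1 by computer") and says that "neither investigators nor participants were blinded; however, trial outcome assessors will be blinded".
- Section 2.11 defines the primary endpoint as a responder proportion ("Overall effectiveness rate is defined as the proportion of patients whose SAS and SDS scores have reduced by more than 25" per cent) and sizes the trial on those who remain: "After accounting for the 20% dropout rate, 296 patients with 148 in each group comprised the final sample size".
- Section 2.12 names tests and software. Neither it nor any other section says that removed women are still followed up, or that they are analysed in the group to which they were assigned.

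**The concern.** Randomisation makes the two groups comparable only as long as they stay whole. Failing to comply, departing from conventional treatment, having an unanticipated event and being judged unfit mainly become known after allocation, and each may be related to anxiety, depression or the course of the pregnancy. If women leave on these grounds, the responder rates compare those who were kept, not those who were randomised.

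Three features make this more than a matter of wording.

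- Investigators and participants know the allocation, and being judged unfit has no stated criterion.
- The arms ask different things of a woman. Section 2.6 describes weekly group calls, weekly information and daily messages; section 2.7 describes routine examinations, booklets and education. One compliance rule may therefore filter the two groups differently.
- Miscarriage, ectopic pregnancy and live birth are secondary outcomes (section 2.8). Section 2.4 does not exempt outcome events from its unanticipated events, so a woman could be removed because she is having an event that the trial is meant to count.

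Removal from the study, read plainly, also ends data collection. An analysis plan written later can define an analysis set, but it cannot recover questionnaires that were never sent.

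**Working it through.** **1. The plan's own figure.** Inputs from section 2.11: 75% v 60%, level 0.05, power 0.80, dropout 20%. With unpooled variance and a one-sided test, n per arm = (1.645 + 0.842)² × (0.75×0.25 + 0.60×0.40) / 0.15² = 117.5, so 118 per arm and 236 in total, as stated. Dropout: 118 / 0.80 = 147.5, so 148 per arm and 296 in total, as stated. The power calculation thus rests on the women left after a 20% loss, which fits an analysis of completers but does not prove that one is planned. (The one-sided basis conflicts with the 2-tailed testing in section 2.12; that is a separate point.)

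**2. When each ground can arise.** Sections 2.5 and 2.9 put eligibility and consent before allocation.

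- Refused permission, and some failures of the inclusion criteria, may come before allocation and then do no harm.
- Non-compliance, departure from conventional treatment, unanticipated events and being judged unfit come mainly after it.

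**3. What removal can do to the responder rate.** The documents give neither removal rates by arm nor outcomes of removed women, so what follows is illustration. Assumptions: no true effect, 60% response in both arms (the control rate of section 2.11), 148 randomised per arm, two-sided 0.05. If a fraction r of an arm is removed and a fraction q of those would have responded, the rate among those kept is (0.60 − r×q) / (1 − r). With r = 0.20 and q = 0.40 this is (0.60 − 0.08) / 0.80 = 0.65.

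| Removed, WeChat / control | Response among removed | Rates among those kept, WeChat v control | False difference (points) | Type I error |
|---|---|---|---|---|
| 20% / 0% | 40% | 65.0% v 60.0% | +5.0 | 13% |
| 0% / 20% | 40% | 60.0% v 65.0% | −5.0 | 13% |
| 20% / 20% | 40% in both | 65.0% v 65.0% | 0.0 | 5% |
| 20% / 10% | 40% in both | 65.0% v 62.2% | +2.8 | 7% |
| 10% / 20% | 40% in both | 62.2% v 65.0% | −2.8 | 7% |
| 20% / 0% | 80% | 55.0% v 60.0% | −5.0 | 13% |
| 20% / 0% | 20% | 70.0% v 60.0% | +10.0 | 39% |
| 0% / 20% | 20% | 60.0% v 70.0% | −10.0 | 39% |

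First row in full: n = 118.4 and 148; pooled rate 0.622; standard error under the null √(0.622×0.378×(1/118.4 + 1/148)) = 0.0598; standard error at the observed rates √(0.65×0.35/118.4 + 0.60×0.40/148) = 0.0595. The chance of rejecting in favour of WeChat is Φ((0.05 − 1.96×0.0598)/0.0595) = Φ(−1.13) = 0.130. The other tail adds about 0.002, giving 0.132.

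Equal numbers removed are not enough for safety. With 20% removed from each arm, but 40% response among the removed in WeChat and 60% in control, the rates are 65.0% v 60.0% and the type I error is 12.5%. The bias vanishes when removal is alike in both number and kind.

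**4. What keeping everyone could cost.** If 20% of each arm give no outcome and are counted as non-responders, the planned rates become 0.75×0.80 = 60% and 0.60×0.80 = 48%. With 148 per arm the two-sided power is Φ((0.12 − 1.96×√(0.54×0.46×2/148)) / √((0.60×0.40 + 0.48×0.52)/148)) = Φ((0.12 − 0.1136)/0.0575) = Φ(0.11), about 54%. The same calculation at 75% v 60% gives 69% with 118 per arm and 79% with 148 per arm.

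**The case against.** The best defence is that removal from the study is not stated to be exclusion from the analysis, and that analysis sets are commonly left to an analysis plan that is not shown here. This stands as far as it goes: the article does not say that outcomes already collected will be discarded, and the lack of a named analysis population is not the complaint. It does not dispose of the point, because the removal rules are stated text in the protocol and a later plan cannot supply follow-up that they cut short.

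A reader might infer more than the documents support.

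- *That the rules favour the intervention as a matter of fact.* No section says which arm would lose more women or how removed women would have fared. The table shows bias of either sign.
- *That only the WeChat arm is filtered.* Both rules apply to all participants, and departure from conventional treatment plainly reaches women in routine care. Section 2.6 puts most duties on the volunteers and sets no participation threshold, so low engagement is not defined as non-compliance. Asymmetry is plausible but not documented.
- *That women who deteriorate are removed.* Section 2.4 answers worsening health with immediate action, not expressly with removal.
- *That the whole 20% is selective removal.* Section 2.3.3 counts voluntary withdrawal as dropout, and section 2.5 lets women leave freely. Those losses would occur under any rule.
- *That unblinded staff take the removal decisions.* Neither section says who decides; section 2.9 says only that investigators and participants are not blinded.
- *That removal for ineligibility is as harmful as the rest.* Removal on baseline facts need not bias the comparison.

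**Conclusion.** The point holds without a fixed direction. Sections 2.3.3 and 2.4 order removal on grounds that mostly arise after randomisation, in a trial with unblinded investigators and participants, and nothing in the article keeps removed women in follow-up or in their assigned group. Carried out as written, this breaks the randomised comparison for the primary responder rate and may also take out women who are having the secondary pregnancy outcomes.

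The size cannot be derived from the documents. Over the assumed scenarios the false difference runs from −10 to +10 points against a target of 15. The central illustration is 5 points either way with type I error about 13%, and there is no bias if removal is alike in both arms. A lean towards WeChat is plausible if non-compliance is concentrated in that arm, but it remains a conjecture. The rule should be changed before the data are affected, since data lost through removal cannot be restored.

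**What to change.** Rewrite sections 2.3.3 and 2.4 so that:

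- stopping the intervention is separate from leaving the study. When a woman should stop the programme is a clinical matter on which this point takes no position;
- every randomised woman stays in electronic follow-up and in the recording of pregnancy outcomes, unless she withdraws consent for her data;
- the primary analysis takes all randomised women in their assigned groups, whatever their compliance;
- the compliant women form a secondary per-protocol analysis.

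The method for outcomes that are still missing can be left to the analysis plan.

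The cost is a change of wording and the sending of the existing electronic questionnaires to women who stop the programme. The effect estimate may be smaller. If missing women are counted as non-responders, power falls to about 54% two-sided when 20% per arm are so counted. Continued follow-up reduces that loss, since fewer women would then be missing.

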### 2.4. Study case discontinuation

Subjects will be removed from the study if they exhibit unusual physiological reactions, experience other unanticipated events, or are deemed unfit to continue taking part in the experiment. In the event that the individual experiences significant issues or if their health worsens, immediate action will be done.

### 2.5. Study population and recruitment

Patients having clinical pregnancies following IVF-ET will start enrolling in the trial. Once clinical pregnancy is confirmed and the inclusion and exclusion requirements are met, patients will receive comprehensive written information regarding the trial methodology and give their signed informed permission. Baseline blood tests, ultrasonography, anxiety and depression rating scales, as well as basic demographic data, will all be completed. After receiving the trial protocol, the researchers will allocate patients to one of the study groups randomly. All participants in the study are free to leave at any moment without providing a reason.

### 2.6. Interventions

Peer support group on WeChat:

Ten women who had received IVF-ET in our center and had given birth at term were chosen as peer support volunteers in the WeChat group. These ladies had good return visit records. Selection criteria include: (1) a happy disposition, the ability to communicate oneself clearly and persuasively, (2) a sound mental condition, as well as strong self-control and self-discipline, (3) completion of primary school or higher, as well as adequate leisure.Ten volunteers underwent training from attending doctors and specialized nurses that covered common illnesses after IVF-ET during pregnancy, interactive skills for using relevant WeChat groups, job responsibilities and team management skills, and knowledge of how to deal with typical psychological issues. Five lessons altogether, lasting between 1 and 2 hours each. Individualized online or offline tuition can be offered depending on the needs of the team leader.A WeChat group called “IVF-ET Peer Support Exchange Group” was created. Its members included 148 subjects, 10 volunteers, an attending physician, and a specialized nurse. According to the participants’ data, volunteers routinely reminded them to have their obstetric exams, provided weekly pregnancy-related information on WeChat’s public account, and disseminated pregnancy advice. Weekly group video/group audio communications offered the subjects emotional assistance. Daily prenatal education music was shared with the participants as well as reminders to lead healthy lives and get enough sleep (this included a nutritious diet, cutting back on late nights, quitting smoking and drinking, and having a happy outlook). At any point during the course of treatment, patients are free to ask questions and express their feelings in the group, and volunteers are there to clear up any confusion. Attending physicians and specialty doctors can offer focused explanations and emotional support when patients feel disputed or bewildered.

